## Abstract

**Background:**

The overlapping epidemics of opioid use disorder (OUD) and HIV present a critical public health challenge. Although people with OUD frequently engage with healthcare settings, uptake of HIV prevention services such as pre-exposure prophylaxis (PrEP) remains low. Integrating HIV prevention into routine OUD care could reduce new infections, but scalable, evidence-based strategies are lacking. Rhode Island offers a unique opportunity to design and evaluate such strategies using its robust data infrastructure and high OUD burden.

**Methods:**

We will conduct a three-phase, sequential implementation study. In Aim 1, we will use the Rhode Island All-Payer Claims Database and State Emergency Department Database data to identify healthcare engagement patterns and gaps in HIV prevention service delivery among people with OUD, including rates of HIV screening, PrEP use, and medications for OUD uptake, across settings from 2012 to 2022. In Aim 2, we will convene a series of five stakeholder-engaged evidence-based quality improvement panels—including with providers, policymakers, and people with lived experience—to co-develop implementation strategies tailored to each care setting (i.e., primary care, mental health clinics, emergency department, and opioid use treatment centers). Finally, in Aim 3, we will develop an agent-based model (ABM) to simulate the population-level effect of implementation strategies developed for each care setting (as identified in Aim 2). The ABM will project outcomes such as HIV incidence, cases averted, and number needed to treat (NNT) over 5- and 10-year horizons under various scenarios. Model parameters will be based on literature and findings from Aim 1. Outputs from the ABM will be used to prioritize feasible, high-impact strategies for future real-world implementation.

**Discussion:**

This study addresses critical gaps in HIV prevention for people with OUD by combining claims-based analysis, evidence-based quality improvement, and agent-based modeling. By leveraging real-world data and engaging diverse stakeholders, the study aims to generate actionable strategies tailored to clinical settings. Findings will inform future implementation efforts in Rhode Island and other jurisdictions facing overlapping HIV and opioid epidemics.

**Trial registration:**

This study does not meet the World Health Organization’s definition of a clinical trial and, therefore, was not registered.

**Supplementary Information:**

The online version contains supplementary material available at 10.1186/s43058-025-00782-1.

Contributions to the literature
This study is the first to leverage statewide All-Payer Claims and Emergency Department data to identify real-world gaps in HIV prevention and medication for OUD uptake—capturing patterns across insured and uninsured populations, and offering critical insights into opportunities for feasible, targeted implementation strategies.Collaborative, evidence-based quality improvement ensures that strategies are co-designed and tailored to the operational realities of clinical settings, enhancing their potential for real-world adoption and sustainability.Agent-based modeling enables simultaneous testing of multiple intervention strategies, reducing the time and resources required for sequential trials, while identifying actionable guidance for real-world implementation and scale-up.

## Background

An estimated 2.7 million people have opioid use disorder (OUD) in the United States (US), and more than 105,000 overdose deaths occurred in 2023 [1]. As the opioid overdose epidemic has worsened, there has been growing concern about opioid use fueling the transmission of infectious diseases, including HIV and hepatitis C virus. An estimated 2.6% of the US population has a history of injection drug use, further underscoring the importance of studying links between OUD and HIV [2]. Opioid use has been associated with several HIV outbreaks in the US since 2015, and approximately 2300 new HIV infections were due to injection drug use in 2022 [3–6]. Despite the availability of effective HIV prevention and intervention strategies, many people with OUD do not receive these strategies in the places where they receive care, highlighting a pressing implementation gap [7].

### Barriers to HIV prevention in OUD care

There are several highly effective, evidence-based public health approaches for HIV prevention: HIV screening, treatment as prevention (TasP), pre-exposure prophylaxis (PrEP), and medications for opioid use disorder (MOUD), including buprenorphine, methadone, and naltrexone. Despite the higher risk of HIV among people with OUD, routine incorporation of HIV prevention services into OUD patient care is remarkably low. Merely 0.8% of emergency department (ED) visits in 2020 and 1.09% of primary care visits from 2009 to 2016 included an HIV test [6, 8]. Additionally, less than a third of patients with OUD are screened for HIV during ED visits, missing a key opportunity for early HIV detection and management [9]. The integration of OUD screening and provisions of MOUD in primary care and EDs has similarly not met expectations due to inadequate provider training, provider reluctance, and limited infrastructure and logistical constraints [10–12]. The implementation of PrEP programs in real-world settings like primary care, EDs, and substance use treatment centers has also been limited. Although one-third of patients in EDs qualified for PrEP under the current Centers for Disease Control and Prevention (CDC) guidelines, only 1.2%-2.2% initiated PrEP as a result of their ED visits [13]. Only 6% of primary care providers have ever prescribed PrEP [14]. Overall, the implementation of HIV prevention services into healthcare settings is complicated by a spectrum of social determinants of health (SDH), such as socio-economic status, stigma, and cultural beliefs at the social level, and other issues including insufficient healthcare infrastructure, insurance challenges, and legal barriers at the structural level [7]. At the provider level, discomfort, stigma, and reluctance to prescribe HIV prevention medications also remain key barriers [12, 15, 16]. Despite the availability of educational resources and simplified prescribing protocols, some providers still avoid offering PrEP and/or MOUD due to persistent biases, limited confidence in managing complex social needs, or concern about ‘enabling’ risky behavior [12, 15, 16].

People with OUD frequently encounter the healthcare system through EDs, primary care clinics, substance use treatment centers, and mental health clinics [17, 18]. Approximately one in every 80 ED visits may be due to opioid-related health issues [19]. The 3-year prevalence of OUD among primary care patients was 0.7–1.4% across seven US health systems between 2014 and 2019 [20, 21]. Approximately one-fifth of people with OUD may also seek out treatment at substance use treatment centers [22, 23]. A significant portion, nearly 60%, of those with OUD also suffer from mild to severe mental illnesses [24]. People with OUD could benefit from an integrated healthcare approach due to their multifaceted health needs, including OUD treatment, mental health care, and HIV prevention; however, the reality is that the healthcare system is fragmented—services like MOUD, mental health services, and HIV prevention care are often delivered across different settings. This disconnection leads to missed opportunities for early intervention and makes it challenging for patients with OUD and/or mental illnesses to remain engaged in PrEP care if they are not concurrently receiving treatment [25, 26].

Rhode Island presents a unique opportunity to address these barriers in HIV prevention among people with OUD through the innovative use of population-level administrative data. The state’s All-Payer Claims Database (APCD), coupled with the State Emergency Department Database (SEDD), enables a comprehensive assessment of insured and uninsured individuals across diverse clinical settings, which could provide important insights into real-world healthcare engagement and service utilization, and offers a foundation for designing and implementing scalable, data-driven interventions.

### Implementation science as a promising approach

Incorporating HIV prevention approaches into a comprehensive public health strategy not only addresses the immediate health needs of at-risk populations, but also contributes significantly to the broader goal of HIV elimination. Currently, there is no comprehensive assessment of the frequency and pattern of healthcare seeking behaviors among people with OUD, which could help inform tailored implementation strategies that involve stakeholder engagement, capacity building, and the creation of context-specific HIV prevention services and MOUD delivery models, determining the optimal locations, appropriate providers (nurses or physicians or others), and the most effective methods for HIV prevention services and MOUD [27, 28].

Implementation science is the study and application of methods to integrate evidence-based practices and policies into routine healthcare [29]. Implementation studies often identify and address multi-level determinants (barriers and facilitators), develop implementation strategies, and evaluate the effectiveness of these strategies in addressing implementation outcomes [29]. Developing implementation strategies that are feasible, specific, and effective is a cornerstone of overcoming multi-level barriers and ensuring successful adoption and sustainment of interventions in HIV and OUD care [28, 30]. One promising approach to developing implementation strategies is through an Evidence-Based Quality Improvement (EBQI) model. EBQI fosters multidisciplinary collaboration, lived experience, and integration of evidence-based change strategies to adapt evidence-based practices to local contexts [31, 32]. The EBQI model has demonstrated effectiveness in adapting clinical practices and fostering strong partnerships between researchers and clinicians, making it a promising framework for developing feasible, specific, and effective implementation strategies to overcome barriers to integrating HIV prevention services in healthcare settings where people with OUD seek care [33, 34].

### Agent-based modeling

Evaluating the effectiveness of implementation strategies in real-world settings can be time-consuming and resource intensive [35]. Agent-based modeling is a powerful tool to test complex approaches, such as implementation strategies, by simulating a collection of decision-making individuals (called “agents”) within a system. These autonomous agents interact with each other and their environment, allowing researchers to explore how individuals of a system behave as a function of individual characteristics and interactions with each other and the environment [36]. Agent-based models (ABMs) have several advantages for studying implementation strategies, including: 1) allowing bi-directional and non-linear interactions between individuals, organizations, and environmental factors; 2) defining dynamic decision-making processes; 3) simulating processes like adoption, negative/positive feedback loops, and relational structures such as social networks; 4) estimating population-level outcomes while accounting for individual-level heterogeneity; and 5) acting as "intervention testing laboratories" when real-world experimentation is infeasible or too costly [37–41]. Several studies in areas such as tobacco control and HIV prevention have successfully employed ABM to estimate the effect of complex interventions to guide implementation decisions for improving the delivery of evidence-based practices [42–46]. However, most of these models focused on transmission dynamics (i.e., how diseases spread within a population) rather than evaluation of the implementation strategies for integrating HIV prevention services into OUD care. ABM offers an innovative approach to test such strategies, especially when informed by stakeholder input and real-world data.

### The current study

This study leverages several innovative approaches to develop and test implementation strategies that overcome barriers to integrating HIV prevention into care settings where people with OUD are already seeking services. Aim 1 analyzes healthcare and HIV prevention service utilization patterns among people with OUD using statewide claims and emergency department (ED) data to identify multi-level barriers in HIV prevention and MOUD uptake among people with OUD. Aim 2 develops feasible and context-specific implementation strategies through stakeholder engagement using implementation science methods nested within an EBQI model. Aim 3 evaluates the population-level impact of developed implementation strategies through agent-based modeling.

## Methods

We followed the *StaRI* (Standards for Reporting Implementation Studies) guidelines when preparing this protocol to ensure completeness and transparency [47]. The completed checklist is included as an Additional file.

### Aim 1 – Claims-based utilization analysis

#### Study design

Aim 1 will employ a retrospective cohort study design to quantify healthcare engagement and HIV prevention service use among people with OUD in RI. This analysis will use Rhode Island All-Payer Claims Database (APCD) and ED data to identify service utilization patterns across different clinical settings from 2012 to 2022. These findings will inform subsequent strategy development and simulation testing in OUD care in Aims 2 and 3.

#### Data sources

We will use two primary data sources to capture insured and uninsured individuals in RI:Rhode Island (RI) All-Payer Claims Database (APCD) includes longitudinal medical and pharmacy claims, participant demographics and enrollment information, and provider characteristics data from private insurers, Medicare, and Medicaid (Table 1). APCD data are updated monthly and reflect over 90% of the insured population in RI (based on our preliminary analysis). We will use APCD data between 2012 and 2022 to evaluate trends over time.Rhode Island State Emergency Department Database (SEDD): Captures encounter-level data for ED visits, including those involving uninsured individuals (estimated 5.0% of RI population, based on 2022 data) [48]. While SEDD lacks unique patient identifiers and pharmacy/provider details, it complements APCD by providing a more complete picture of ED utilization among patients who may be excluded from claims-based analyses. Because SEDD does not allow for longitudinal tracking of individuals across visits, these data will be used to characterize encounter-level trends among the uninsured population. APCD and SEDD will not be linked at the individual level; however, each will be analyzed separately but interpreted together to capture utilization across the full population of people with OUD.

**Table 1 Tab1:** Data variables for statistical analysis in Aim 1

Demographic data	Medical care information	Provider information
Age Sex ZIP Code City Insurance information Relationship to health policyholder Internal unique identifier	Date of service Type of service Location of service Date prescription(s) filled ICD-9/10 diagnostic codes National Drug Code Prescription refill indicator Pharmacy ID Inpatient and outpatient claims Mental health claims	Practice Attending provider name Prescribing provider name Type Primary care indicator Specialty Address ZIP Code City Pharmacy ID

#### Study population

The study population will consist of people who are: 18 years of age or older, residing in Rhode Island during health insurance enrollment, and presented evidence of OUD (see OUD criteria below), between 2012 and 2022. To ensure robustness of findings, we will include only individuals who had 6 months of continuous health insurance coverage after their first OUD-related claim within a calendar year. People with OUD will be identified in APCD using one or more of the following:International Classification of Diseases (ICD-9/10) diagnosis codes for OUD, encompassing diagnostic codes for opioid use, opioid abuse, and opioid dependence.Healthcare Common Procedure Coding System (HCPCS) and Current Procedural Terminology (CPT) codes for OUD-related services, including OUD treatment administration (e.g., injection and oral medication administration).National Drug Codes (NDCs) for MOUD, including various forms (e.g., injection and medication), dosages, strengths, and formulations (e.g., branded and generic) of methadone, buprenorphine, and naltrexone.

The study cohort will include individuals with at least one qualifying encounter or prescription during the study period. A supplemental table (Table S1) will provide the complete list of codes used for cohort identification.

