**Fig. 1 Fig1:**
[figure not shown]
Overview of three aims in our study

In particular, we will assess receipt of HIV prevention services, including HIV testing and PrEP, as well as MOUD. We will use CPT codes (86,689, 86,701–86703, 87,534–87,536, 87,390) and HCPCS codes (G0432–G0435) to identify claims for HIV testing. PrEP use will be defined as having a prescription for a 30-day or longer supply of tenofovir/emtricitabine or tenofovir alafenamide/emtricitabine, without a concurrent diagnosis of HIV or hepatitis B virus. MOUD receipt will use the definitions stated above, based on NDC and procedure codes. All utilization outcomes will be summarized and stratified by care setting and insurance type where applicable. We will also explore temporal trends across the study period.

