**Fig. 2 Fig2:**
[figure not shown]
Flowchart of retrospective data analysis in Aim 1

In descriptive analysis, we will summarize annual frequencies and rates of healthcare utilization and HIV prevention service uptake by setting and insurance status. Results will be stratified by age group, gender, race/ethnicity, and geographic region. Statistical tests (e.g., Chi-square, t-test, and ANOVA) and trend analyses will be used to examine differences in service utilization across years and subgroups.

In regression modeling, we will fit multivariable logistic regression models to identify individual- and area-level factors that are associated with receipt of HIV testing, PrEP uptake and retention, and MOUD initiation and retention (defined as continuous MOUD coverage for 180 days, permitting gaps no longer than 7 days) [49]. Covariates will include demographic characteristics (age, gender, race/ethnicity), insurance type, healthcare setting, and SDH indicators (e.g., housing instability, incarceration). Area-level variables from the U.S. Census Bureau (i.e., American Community Survey) will be linked to each individual via zip codes. If data structure allows, we will implement multilevel models to account for clustering at the geographic level. We will report adjusted odds ratios (aORs) with 95% confidence intervals. We will conduct several sensitivity analyses with alternate definitions of PrEP use and retention (e.g., 60-days of supply, and allowing for various lengths of gaps between refills). All analyses will be conducted using SAS 9.4. Statistical significance will be assessed at the *p* < 0.05 level unless otherwise specified.

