#### Outcome definition

The base model will represent the status quo—current levels of HIV prevention service delivery across different care settings, as established through Aim 1. Using Python™, we will evaluate the effect of each proposed implementation strategy (developed in Aim 2) on multiple outcome measures over 5- and 10-year projections.

Key outcomes will include projected HIV incidence across the population, as well as the number of new HIV cases averted or caused relative to the base model. We will also assess changes in healthcare utilization patterns and quantify uptake of PrEP and MOUD by setting. For each intervention scenario, we will calculate the number needed to treat (NNT)—defined as the number of HIV prevention service encounters or MOUD prescriptions required to prevent a single HIV infection over a specified time horizon. And lastly, the model will assess the population-level impact of integrating HIV prevention services into OUD care. These outcomes will guide the selection of the most effective and feasible strategy package for real-world implementation and inform the prioritization of approaches for future pilot testing and scale-up.

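### Six months of coverage after the first OUD claim of the year cannot be shown for late-2022 claims, so on the natural reading 2022 holds a differently selected cohort

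*Protocol article*

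**What the plan says.** The inclusion rule is in the protocol article, Methods, Aim 1, Study population: "we will include only individuals who had 6 months of continuous health insurance coverage after their first OUD-related claim within a calendar year". The same section adds: "The study cohort will include individuals with at least one qualifying encounter or prescription during the study period". Qualifying codes include MOUD prescriptions and MOUD administration.

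Data sources sets the period: "We will use APCD data between 2012 and 2022 to evaluate trends over time". It also says that "APCD data are updated monthly and reflect over 90% of the insured population in RI", but plans no use of records after 2022.

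The years are then compared. Outcome measures says "We will also explore temporal trends across the study period". The Aim 1 Analysis plan says "we will summarize annual frequencies and rates of healthcare utilization and HIV prevention service uptake by setting and insurance status", and adds statistical tests of differences across years. That section also has a look-forward outcome, MOUD retention, "defined as continuous MOUD coverage for 180 days, permitting gaps no longer than 7 days".

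Aim 3, Outcome definition, takes its baseline from these results: "The base model will represent the status quo—current levels of HIV prevention service delivery across different care settings, as established through Aim 1". It names no year.

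**The concern.** Two stated rules collide at the end of the data. In 2012–2021, someone whose first OUD claim of the year is in October can qualify on coverage that runs into the next year. In 2022 that coverage lies outside the stated data. This happens even if nobody loses insurance, so it is separate from selection on staying insured.

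The loss is not random. A patient with monthly MOUD fills has a first OUD claim early in the year and is kept. A patient with one sporadic contact may well have it in the second half of the year and be dropped. Because MOUD is both a route into the cohort and an outcome, the entry rule itself would push 2022 MOUD receipt upwards. A fall in the number of people with OUD, or a step in annual rates, between 2021 and 2022 could then be an artefact of the entry window.

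**Working it through.** The plan states no figure for this point, so there is none to reproduce. The check is date arithmetic followed by an illustration under stated assumptions.

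**Last 2022 index date.** Inputs are a six-month look-forward (Study population) and data ending in 2022 (Data sources), taken as 31 December. Last eligible date = 31 December 2022 minus the look-forward:
- 184 days: 30 June
- 183 days: 1 July
- 180 days: 4 July

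**Evenly spread first OUD claims.** The share of 2022 index dates lost is 49.3% (180 days) to 50.4% (184 days), or about half.

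**Loss by claim frequency.** The document gives no claim rates, so L claims a year with Poisson timing is an assumption. The share with a first OUD claim in July–December, given at least one claim in the year, is

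(e^(−L/2) − e^(−L)) / (1 − e^(−L))

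| L (claims/year, assumed) | Share lost in 2022 |
|---|---|
| 0.5 | 43.8% |
| 1 | 37.8% |
| 2 | 26.9% |
| 4 | 11.9% |
| 6 | 4.7% |
| 12 | 0.25% |

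**Effect on case mix, with everyone re-qualifying each year.** Assume equal numbers of people at 12 claims and at 1 claim a year.
- Full year: 1 − e^(−12) ≈ 1.000 of frequent users and 1 − e^(−1) = 0.632 of rare users enter. Frequent-user share = 1.000/1.632 = 61.3%.
- January–June only: 1 − e^(−6) = 0.998 and 1 − e^(−0.5) = 0.393 enter. Frequent-user share = 0.998/1.391 = 71.7%.
- Cohort size ratio = 1.391/1.632 = 0.852, a fall of about 15% with no real change.
- If uptake of a service were 30% in frequent and 10% in rare users (assumed), the observed rate would move from 0.10 + 0.20 × 0.613 = 22.3% to 0.10 + 0.20 × 0.717 = 24.3%.

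**Effect by share of new entrants.** Assume entrants with evenly spread first OUD claims form a share s of a normal year, and the rest have 12 claims a year. The loss is 0.504s + 0.0025(1 − s), and the entrant share becomes 0.496s/(1 − loss).

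| s (assumed) | Cohort lost | Entrant share in 2022 |
|---|---|---|
| 10% | 5.3% | 5.2% |
| 20% | 10.3% | 11.1% |
| 30% | 15.3% | 17.6% |
| 50% | 25.3% | 33.2% |

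**Direction.** If a service were instead more common in new entrants (assumed 30% against 15%), then at s = 20% the full-year rate is 0.30 × 0.20 + 0.15 × 0.80 = 18.0%, and the 2022 rate is 0.30 × 0.1106 + 0.15 × 0.8894 = 16.7%. The sign reverses.

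**Other reading.** If the six months must lie inside the same calendar year, the cut-off is about 1 July in every year from 2012 to 2022, and 2022 does not stand out.

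**MOUD retention.** A treatment start after about 4 July 2022 does not have 180 days of claims left in the data.

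**The case against.** The inclusion sentence is ambiguous. Under the same-calendar-year reading, no year differs from another. That stands, and it is why the point is conditional. It does not remove the need for action, since every year would then silently exclude most second-half first OUD claims.

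The cohort may be defined per person over the whole period, so that someone who qualified in 2018 stays in when the first 2022 claim comes in October. The loss would then fall only on people whose sole chance to qualify is late 2022. This also stands. The case-mix illustration applies annual re-qualification to everyone and would overstate the loss.

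The stated period may describe the analysis rather than the extract, and the database is updated monthly. A condensed article could leave an enrolment run-out to the full protocol. That is possible, but no run-out is stated, and the rules as written produce the edge.

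Two stronger conclusions are tempting. A reader might infer that HIV testing and PrEP rates will also appear to rise in 2022. The document does not say that either goes with OUD-claim frequency, and the direction check shows that the sign can reverse. A reader might also infer that the simulation baseline is distorted and understates the gap in services. Outcome definition names no year, calibration uses historical trends, and the sensitivity analyses vary every parameter, so use of 2022 alone is not established.

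**Conclusion.** The point holds conditionally. It rests on two conditions: the calendar-year phrase identifies the first OUD claim of each year, which is the more natural reading, and no enrolment data after December 2022 are used. The 2022 cohort is then limited to first OUD claims up to about 1–4 July, while earlier years admit all twelve months, and it enters the annual rates and tests across years without separate handling.

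The size cannot be fixed from the document. Under the assumed claim rates it runs from negligible for monthly users to about half of evenly spread new entrants, and it shrinks if earlier qualifiers are retained. An upward shift is well supported for MOUD receipt only. A carry-over to the model's status quo is a risk to close off, not a demonstrated error.

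**What to change.** In Aim 1, Study population, state which reading applies and whether people re-qualify each year. Then make the entry window the same for all years compared, in one of three ways:
- obtain enrolment records to June 2023 and use them solely to check coverage for late-2022 entrants;
- end the annual trend at 2021;
- compare 2022 only with January–June entrants of earlier years.

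The enrolment extract alone does not repair MOUD retention. Report that outcome only for starts with 180 days of claims in the data.

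In Aim 3, Outcome definition, name the Aim 1 year or years used for the status quo, and do not use a truncated 2022 cohort alone.

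The cost is a few sentences, plus either one lost trend year or a small extra enrolment extract. The third option loses no year but sets aside second-half entrants of earlier years in that comparison.

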#### Outcome measures

We will assess healthcare utilization across four types of care settings, including ED, primary care, substance use treatment center, and mental health service facility (Fig. 1).ED visits will be identified in APCD using HCPCS (99,281–99,285) and revenue codes (0450–0459, 0981). Uninsured ED visits will be identified in SEDD using OUD and MOUD diagnosis codes. Given the lack of unique identifiers in SEDD, each record represents a single encounter.Primary care visits will be identified using CPT codes for outpatient visits (9201–99215, 99,381–99,397), HCPCS code T1015, and provider specialty codes (01, 08, 11, 19, 31, 38, 50, 84, 97) indicating primary care (e.g., internal medicine, family medicine, nurse practitioners, physician assistants).Substance use treatment visits will be identified via CPT codes for substance use services (e.g., H0015, H0018, H0020), including MOUD-related services. Claims will be restricted to facilities verified as SAMHSA-regulated Opioid Treatment Programs (OTPs) in Rhode Island. We recognize that office-based MOUD services are increasingly provided in primary care and other outpatient settings; however, these visits will be captured under the primary care setting definition.Mental health service visits will be identified using CPT codes (90,791–90853, 99,404) and provider taxonomy for psychiatry, psychology, and behavioral health providers.

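### One claim, even one carrying only an opioid-use code, makes a person an OUD case, and no stated Aim 1 sensitivity analysis tests that rule

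*Protocol article*

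**What the plan says.** Aim 1, Study population, gives three routes into the APCD cohort: diagnosis codes, procedure codes for OUD services, and drug codes for MOUD. Any one suffices: "People with OUD will be identified in APCD using one or more of the following". The diagnosis route is described as "encompassing diagnostic codes for opioid use, opioid abuse, and opioid dependence", and the cohort takes in "individuals with at least one qualifying encounter or prescription during the study period". The one further condition tied to the index claim is "6 months of continuous health insurance coverage after their first OUD-related claim within a calendar year". For the codes themselves the section points to a supplement: "A supplemental table (Table S1) will provide the complete list of codes used for cohort identification".

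For uninsured people the rule works on encounters (Aim 1, Outcome measures): "Uninsured ED visits will be identified in SEDD using OUD and MOUD diagnosis codes".

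The Aim 1 Analysis plan names its sensitivity analyses: "We will conduct several sensitivity analyses with alternate definitions of PrEP use and retention". None concerns the OUD definition. The Limitations section does not list wrongly classified OUD cases among the weaknesses of claims data.

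The results travel on. Session 1 of Aim 2 shows them to the panel. In Aim 3, Outcome definition takes the status-quo service levels from Aim 1, Model input uses Aim 1 along with the literature for agent traits, and Model calibration and validation takes some targets from Aim 1, with ED use as the example.

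**The concern.** The target is a disorder, but the rule accepts one code for use without abuse or dependence, once, in any setting. The coverage condition checks enrolment and does nothing to confirm the diagnosis. Some cohort members may therefore not have OUD.

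The cohort is the denominator for MOUD receipt, HIV testing and PrEP, reported by care setting. Entry and outcome are also linked for MOUD: a person admitted by a MOUD code counts as a recipient by construction, while a person admitted on one opioid-use code does not. The reported MOUD rate thus depends on the mix of entry routes, which no stated analysis examines.

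At stake is how much of the service gap shown to the panel, and built into the ABM base case, reflects the case rule rather than care. The planned sensitivity analyses probe one outcome definition and leave the shared denominator alone.

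**Working it through.** The plan has no figure to reproduce: it gives no predictive value, no false-positive share and no expected service rate. All values below are assumptions, chosen to show how the error behaves.

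**Formula.** Let f be the false-positive share of the cohort and r the service rate in false positives divided by the rate in true cases. For a rate over the whole cohort:

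observed / true = (1 − f) + f × r

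| f | r = 0 | r = 0.5 | r = 1 | r = 1.5 |
|---|---|---|---|---|
| 5% | 0.95 | 0.975 | 1.00 | 1.025 |
| 20% | 0.80 | 0.90 | 1.00 | 1.10 |
| 40% | 0.60 | 0.80 | 1.00 | 1.20 |

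The rate falls if false positives use the service less than true cases, is unbiased if they use it equally, and rises if they use it more.

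**MOUD receipt.** For people who enter on a diagnosis code alone and have no OUD, r near 0 is plausible. With a true rate of 50%:
- f = 5%: 0.50 × 0.95 = 47.5%
- f = 20%: 0.50 × 0.80 = 40%
- f = 40%: 0.50 × 0.60 = 30%

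A false positive who enters by a MOUD drug code works the other way, because that person counts as a recipient.

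**HIV testing and PrEP.** Nothing in the article indicates r for these services, so the sign is open.

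**What drives f.** Let s be the share of the cohort whose entry rests on a single diagnosis claim, and PPV the proportion of those who are true cases. If errors arise only there, f = s × (1 − PPV). With s = 30% and PPV = 90% to 70%:
- f = 0.30 × 0.10 = 3%, up to 0.30 × 0.30 = 9%
- a 50% MOUD rate (r = 0) appears as 0.50 × 0.97 = 48.5%, down to 0.50 × 0.91 = 45.5%
- the OUD count is overstated by 1/0.97 − 1 = 3%, up to 1/0.91 − 1 = 10%

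The article gives neither s nor PPV.

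**MOUD retention.** The Analysis plan does not state its denominator. Among recipients, an assumed 40% stays 40% at every f, since a non-recipient is not counted. Over the whole cohort, 0.50 × 0.40 = 20% becomes 19%, 16% and 12% at f = 5%, 20% and 40%.

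**Comparison of settings.** If f were 5% in one setting and 20% in another (r = 0, both truly 50%), the settings would show 47.5% and 40%. The article does not say that f differs by setting; a stricter cohort reported by setting would show whether the comparison depends on the rule.

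**The case against.** The strongest reply is that nothing here is contradictory. The rule is clear, a broad definition is defensible in a population with irregular contact with care, and this is a condensed article: Table S1 and any fuller plan are not shown and might contain a stricter cohort. That stands as a limit on the point. Against it, the article itself fixes the case rule and names its Aim 1 sensitivity analyses, and Table S1 is announced as a code list, not as an alternative rule.

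A second reply is that the Aim 3 Sensitivity analysis varies every model parameter. It does, one at a time at first and then the most influential ones jointly. But a change of case rule moves several Aim 1 inputs together, and varying ABM parameters leaves the Aim 1 rates, the odds ratios and the panel's material untouched.

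A reader might infer more than the article supports:
- That every Aim 1 rate is too low. Retention among MOUD recipients is not diluted by this route, the sign for testing and PrEP is unknown, and SEDD is a separate encounter-level analysis.
- That the single-claim predictive value can be applied to the whole cohort. With PPV of 70% to 90% this would turn a 50% MOUD rate into 35% to 45% and overstate the OUD count by 11% to 43%. It holds only if every member entered on a single claim (s = 100%), which the article does not say.
- That Aim 1 counts set the size of the ABM population. No section says so; agent traits also draw on the literature, and calibration also targets HIV incidence.

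A stricter rule can also bias. Asking for two claims selects on contact with care, which Aim 1 measures, and accepting a single code only from ED or inpatient claims would favour one of the settings being compared. The fix has to avoid the second and acknowledge the first.

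**Conclusion.** The point holds in a limited form. A single claim, including one with only an opioid-use code, makes a person an OUD case, and the article states no analysis that varies this. APCD rates and regressions over the full cohort, and the ABM inputs and calibration targets taken from them, may be distorted by an unknown amount. Dilution is likely for MOUD receipt among diagnosis-code entrants; no direction can be given for HIV testing or PrEP.

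The figures above rest on assumed f, r, s and PPV and only illustrate the range. That a material share of the cohort is false positive is a possibility that the article leaves untested, not something it shows. The change should be made because the data to test it are already held, but the broad definition is not an error in itself.

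**What to change.** Keep the broad definition as primary. Add to the Aim 1 Analysis plan a sensitivity analysis that repeats the APCD rates and regressions:
- (a) without people who qualify only through opioid-use codes;
- (b) requiring, for those who enter by diagnosis code, two claims on different dates, with the same rule in all four care settings.

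Table 1 already lists the fields needed: diagnosis codes, service dates and a unique identifier. In SEDD apply only (a), because without patient identifiers a second claim cannot be matched to the first. State the denominator of MOUD retention at the same time.

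In the Aim 3 Sensitivity analysis, use the broad and strict rates as the range for the corresponding ABM inputs and move them together. A full recalibration is not needed; the calibration targets then stay on the broad definition, which should be said when the range is reported.

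The cost is modest extra analysis and a smaller strict cohort. Under (b) that cohort is tilted toward people with more contact with care, which is why it belongs in a sensitivity analysis and not in the primary one.
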